### Provisions for post-trial care {30}

After study completion, patients will continue to receive standard care for CIDP. Patient who are stable will not require additional treatment. Patients who reach a preliminary endpoint, defined as deterioration during the 18-week treatment period requiring additional CIDP treatment, no improvement at week 18, restart CIDP treatment for any reason (i.e. a relapse) between week 18–52 or drop out during study for whatever reason will be treated at physician’s discretion and will complete follow-up visits according to protocol. AMC Medical Research BV (AMR) has an insurance which is in accordance with the legal requirements in the Netherlands (Article 7 of the Medical Research Involving Human Subjects Act (WMO) and the Measure regarding Compulsory Insurance for Clinical Research in Humans of 23 June 2003). This insurance provides cover for damage to research patients through injury or death caused by the study for patients in the Netherlands. Where harm to participants arises from the conduct of the research, National Health Services (NHS) indemnity applies. Where harm to participants comes from the design or management of the research, this comes under Sponsor insurance. These arrangements are covered in a coordinator agreement and in the site agreements.

### Outcomes {12}

#### Primary outcome

The primary outcome is the number of patients in remission at 52 weeks after start of treatment. Remission is defined as sustained improvement without the need for further treatment. Improvement is defined as improvement by at least the minimal clinical important difference (MCID) on the inflammatory Rasch-Overall Disability Scale (I-RODS) and/or improvement of one or more points on the adjusted Inflammatory Neuropathy Cause and Treatment Disability Scale (INCAT-DS) at 18 weeks (end of treatment) compared to baseline. For the I-RODS, MCID is calculated using a statistical approach in which an increase of 1.96 SE is considered relevant improvement [12]. For the adjusted INCAT-DS, a decrease of 1 point or more is considered a relevant improvement [13, 14]. Changes in upper limb function from ‘0’ (normal) to ‘1’ (minor symptoms) or from ‘1’ to ‘0’ are not considered relevant deterioration or improvement [13]. Sustained is defined as no deterioration between 18 and 52 weeks, i.e. difference on the I-RODS of less than the MCID difference and/or less than one point on the adjusted INCAT-DS. Patients will be considered a treatment failure if they (1) received additional CIDP treatment during the 18-week intervention period, (2) do not improve at 18 weeks, (3) restart CIDP treatment for any reason between 18 and 52 weeks, or (4) do not show a sustained improvement at 52 weeks as defined above.

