**Methods:**

An international, randomised, double-blind, placebo-controlled trial, in adults with ‘probable’ or ‘definite’ CIDP according to the EFNS/PNS 2010 criteria. Three groups of patients are included: (1) treatment naïve, (2) known CIDP patients with a relapse after > 1 year without treatment, and (3) patients with CIDP who improved within 3 months after a single course of IVIg, who subsequently deteriorate at any interval without having received additional treatment. Patients are randomised to receive 7 courses of IVIg and 1000 mg intravenous methylprednisolone (IVMP) (in sodium chloride 0.9%) or IVIg and placebo (sodium chloride 0.9%), every 3 weeks for 18 weeks. IVIg treatment consists of a loading dose of 2 g/kg (over 3–5 days) followed by 6 courses of IVIg 1/g/kg (over 1–2 days). The primary outcome is remission at 1 year, defined as improvement in disability from baseline, sustained between week 18 and week 52 without further treatment. Secondary outcomes include changes in disability, impairment, pain, fatigue, quality of life, care use and costs and (long-term) safety.

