### Participant timeline {13}

Total follow-up is 104 weeks (2 years). After the intervention period of 18 weeks, patients will be followed for another 86 weeks during which treatment will be given only in case of deterioration by at least the MCID on the I-RODS and/or deterioration (i.e. increase) of at least one point on the adjusted INCAT-DS. Choice of treatment in case of relapse is at discretion of the treating physician. If a change of treatment regimen is regarded necessary during the 18 weeks’ intervention period, trial medication will be stopped but further follow-up will continue as scheduled. Additional (ad hoc) visits, i.e. if a relapse is suspected, can be scheduled at discretion of treating physician. Treatment protocol and follow-up are illustrated in Fig. 1.

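### The rule for sustained improvement joins its two stability conditions with and/or, so an untreated deterioration on one scale can be scored as remission

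*Protocol article*

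**What the plan says.** Under Outcomes {12}, Primary outcome, the endpoint is binary: "The primary outcome is the number of patients in remission at 52 weeks after start of treatment". A patient must improve by week 18 on the I-RODS and/or the adjusted INCAT-DS, and the improvement must last. The definition of lasting has two parts. The first is a label: "Sustained is defined as no deterioration between 18 and 52 weeks". The second spells the label out as a "difference on the I-RODS of less than the MCID difference and/or less than one point on the adjusted INCAT-DS".

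Four failure criteria follow. Two matter here. Criterion (3) makes a failure of patients who "restart CIDP treatment for any reason between 18 and 52 weeks". Criterion (4) makes a failure of those who "do not show a sustained improvement at 52 weeks as defined above", which refers back to the clause just quoted.

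Participant timeline {13} describes the change after week 18 that opens the way to treatment as "deterioration by at least the MCID on the I-RODS and/or deterioration (i.e. increase) of at least one point on the adjusted INCAT-DS". The Discussion explains that both scales were chosen because one scale alone can overlook meaningful change.

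**The concern.** And/or is the right connector for improvement on either scale and for deterioration on either scale. It is the wrong connector for the absence of deterioration, which requires that neither scale has crossed its threshold. The clause keeps and/or for the negated condition, so its literal meaning no longer matches its own label.

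The clause decides success or failure on the primary outcome. It also carries into remission at week 104 (Long-term efficacy and safety evaluation) and into cost per additional patient in remission (Economic evaluation). Someone will have to program it, and the missing-data section has imputed scale scores feeding into the primary outcome. Two programmers could code it differently, and the choice should not still be open once outcome data are being analysed.

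**Working it through.** **1. The two rules side by side.** Take a patient who improved at week 18, with change measured from week 18. Worse means past the threshold on that scale.

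| I-RODS | INCAT-DS | Sustained, literal and/or | Sustained, both scales required | Deterioration per Participant timeline |
|---|---|---|---|---|
| stable | stable | yes | yes | no |
| worse | stable | yes | no | yes |
| stable | worse | yes | no | yes |
| worse | worse | no | no | yes |

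The literal clause conflicts with the Participant timeline in the two middle rows. Requiring both scales removes the conflict in every row.

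**2. Who can be misclassified.** Criteria (1) to (3) do not depend on the clause. They remove patients given additional treatment before week 18, patients not improved at week 18, and patients who restarted treatment between weeks 18 and 52. What remains is week-18 improvers who worsened on exactly one scale and were not retreated by week 52. This group can occur:
- The Participant timeline allows treatment "only in case of deterioration by at least the MCID on the I-RODS and/or deterioration (i.e. increase) of at least one point". That sets a condition for treating and does not oblige anyone to treat.
- Table 1 has no scheduled visit between weeks 24 and 52, so worsening can first be recorded at week 52, before any restart.
- The unblinding section, in the week-18 context, already foresees failures who go without further treatment.

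**3. Direction.** The clause says difference, not worsening. If and/or were changed to and with nothing else altered, a patient who kept improving past the threshold on one scale would fail the condition.

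**4. The plan's sample size.** Inputs from Sample size {14}: 0.35 versus 0.65, two-sided 0.05, 80% power, chi-square test. With pooled null variance and mean proportion 0.50:

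n = [1.960·√(2·0.50·0.50) + 0.8416·√(0.35·0.65 + 0.65·0.35)]² / 0.30² = (1.386 + 0.568)² / 0.09 ≈ 42.4, so 43 per arm.

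Power at 43 per arm is 80.6%. Attrition: 43/0.90 = 47.8, so 48 per arm and 96 in total. The odds ratio is (0.65/0.35)/(0.35/0.65) = 3.45. All figures agree with the protocol, and none depends on the connector.

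**5. Can the effect be sized?** The document gives no rate of untreated one-scale deterioration, so every share below is an assumption. Power is at 43 per arm.

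| Assumption | 5 | 10 | 15 |
|---|---|---|---|
| 35%/65% hold under the strict rule; literal rule adds this many points to both arms | 81% | 82% | 84% |
| Same, but points added to the control arm only | 65% | 46% | 29% |
| 35%/65% hold under the literal rule; strict rule removes this percentage of remissions in each arm | 76% | 72% | 67% |

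For the last row, the rates become 0.35(1−q) and 0.65(1−q): 33.25/61.75, 31.5/58.5 and 29.75/55.25 percent. The rows disagree even on whether power rises or falls, and the document does not say which applies.

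**The case against.** The strongest reply is that the intended meaning can be recovered. The label says no deterioration, the Participant timeline puts deterioration on either scale, and the Discussion explains why two scales are needed. On that view this is a slip of wording and nobody chose to count one-scale worsening as remission. That is probably right about intent. It does not settle the matter, because the explanatory clause is the only operational rule, criterion (4) refers back to it, and no other section overrides it.

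The reply that few patients are affected also stands, for the reasons in step 2 of the working.

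Two stronger readings are tempting, and the document supports neither.

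- A reader might infer that the wording dilutes the treatment effect and costs power. If a share f of all failures became remissions in both arms, the difference would be (0.65 + 0.35f) − (0.35 + 0.65f) = 0.30(1 − f), and power would fall to 76% at f = 5% and 53% at f = 30%. But f has no source. It is also applied to failures who cannot be reclassified: non-improvers and everyone treated or retreated. Other assumptions give no loss.
- A reader might infer that anchoring stability to week 18 contradicts the abstract, since a patient could gain one MCID, lose almost all of it, and still be in remission. The abstract defines remission as "improvement in disability from baseline, sustained between week 18 and week 52 without further treatment". That fits improvement judged at week 18 and then held, and does not require the improvement criterion to be met again at week 52. Adding that requirement would create a stricter endpoint, not correct an error.

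**Conclusion.** The clause is wrong as written. Followed literally, it scores as remission a change that another section of the same protocol calls deterioration, on the primary outcome. The conclusion rests on the logic of the two passages and needs no assumption about rates.

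Its reach is limited to week-18 improvers who worsen past the threshold on exactly one scale and are not retreated by week 52. How many there will be, how they will divide between arms, and whether the treatment difference would shrink or grow cannot be determined from the document. The sample size is sound and needs no change. The strict reading was very likely intended, but the primary outcome needs one reading fixed before unblinding.

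**What to change.** For scoring, define sustained as an I-RODS worsening of less than the MCID **and** an adjusted INCAT-DS worsening of less than one point, both compared with week 18. Keep the existing exception for upper-limb changes between 0 and 1. Using worsening in place of difference supplies the missing direction. State that the same rule determines remission at week 104. If the analysis plan, which is not shown here, already fixes this reading, bring the protocol wording into line with it.

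The change concerns classification only and leaves decisions about when to treat untouched. Both scales are already collected at weeks 18, 52 and 104, so no new data are needed. The costs are one sentence, submitted through the protocol's usual amendment route while the trial is blinded, and possibly slightly lower remission counts. If the team also wants to know how many patients still meet the improvement criterion against baseline at week 52, that can be reported as a sensitivity analysis without altering the primary outcome.

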## Discussion

The OPTIC trial is a randomised controlled trial aiming to determine whether combined induction treatment of IVIg and IVMP leads to more remissions than IVIg treatment alone. The trial was designed with IVMP as add on treatment, as most physicians and patients prefer IVIg treatment instead of first-line corticosteroids due to its rapid mode of action and side effect profile. Alternative designs, such as IVMP treatment as standard treatment and randomisation to IVIg/placebo as add on treatment, or an IVIg versus IVMP head-to head comparison, would have reduced feasibility of including sufficient patients due to expected reluctance of patients to participate. A trial directly comparing IVIg and IVMP, with a different primary outcome and inadequate power to assess differences in remission rates, has been performed previously and these long-term remission data contribute to the rationale of the current study [9, 30]. In addition, given the expected difference in time to improvement and possibility of unblinding due to corticosteroid AEs, the design of a head-to-head comparison with a primary outcome of remission would be challenging, as patients not improving in the first 1–2 months will probably drop out of the study to be treated with IVIg. This would lead to a relatively large group stopping with corticosteroids and insufficient exposure to corticosteroids to achieve remissions, as seen in the previously mentioned study [9]. Finally, a 3-arm study of IVIg, IVMP and combined IVIg and IVMP would probably provide the best evidence and guidance, but this design would have the same challenges of including sufficient patients and of early drop-out, and was not regarded feasible in this rare disease. The IVIg regimen is a shortened version of the treatment protocol in the largest IVIg trial in CIDP [13]. This IVIg treatment protocol was chosen to limit potential efficacy concerns in the control group, which may arise from different local IVIg protocols. Local protocols vary in dosing regimens, intervals and dose tapering or withdrawal strategies. It is likely that some patients are overtreated with IVIg in this 18-week treatment protocol, as some patients may only require a single loading dose or maintenance treatment at a lower dose than 1 g/kg [31]. We aim to limit potential overtreatment by stopping treatment after 18 weeks, but if the combined induction treatment proves superior, one could consider individualising treatment by shortening the IVIg treatment and/or reduce the dose regimens depending on treatment response. The primary outcome, remission at 52 weeks, is measured using the I-RODS and the adjusted INCAT-DS. We chose to include both outcome measures to assess disability as relevant changes may be missed in patients if only one of these is used, as was shown in both the IVIg withdrawal as well as subsequent restabilization phase of the PATH study, which used a combination of both outcome measures to assess relevant changes [32, 33]. Combining two outcome measures and using a(n individual) MCID-based approach, we hope to limit potential delay when treatment is required in the event of a relapse. Precautions have been taken to limit potential side effects and unblinding, such as excluding significant cardiovascular co-morbidity and diabetes from enrolment. Potential synergistic effects of IVIg and IVMP regarding (S) AEs have not been previously mentioned in CIDP studies. A study comparing the addition of IVMP/placebo to IVIg in Guillain-Barré syndrome (GBS) did not report significant differences in (S) AEs between the two treatment arms [34]. All patients in the Netherlands will be treated with co-medication to reduce the chance of corticosteroid-induced osteoporosis. In the UK, only patients at risk will be offered co-medication (regardless of subsequent treatment allocation), following national guidelines. This is based on the fracture risk assessment (FRAX score) and counselling regarding the side effects of alendronate acid. We excluded several patient categories for safety reasons (risk of thrombosis) and high risk of unblinding (diabetes). If the combination treatment proves superior, this treatment could be considered in patients that are currently excluded, if AEs due to IVIg and/or corticosteroids are considered manageable. The OPTIC trial started enrolling participants in February 2018. Due to protracted legal negotiations and institutional review board (IRB)/MREC approval, study start was delayed in some Dutch centres as well as in the UK. In the UK, study was approved by the MHRA (Medicines and Healthcare products Regulatory Agency UK) on 29 March 2019, the South Central – Oxford REC 10 May 2019 and by the Health Research Authority (HRA) and Health and Care Research Wales (HCRW) 16 May 2019. This has resulted in a slower rate of inclusion than anticipated. Overall, most eligible patients screened for the study who meet the inclusion criteria are willing to participate in the study. Screen failures are predominantly due to the presence of diabetes, which is an exclusion criterion, or previously administered treatment. As this trial focuses on patients with active disease, instructing non-participating and referring hospitals not to start treatment for CIDP is probably one of the biggest challenges to ensure a steady rate of inclusions. Regarding trial oversight, monitoring of visits so far did not report any operational issues regarding data quality and collection or protocol adherence. The DSMB, after an SAE and after unblinded review of safety data following the first 20 inclusions, did not advise any changes to study management or safety measures. During the course of the study, five amendments were made to the protocol and overall conduct of the study. The first amendment (approved 25 May 2018) added a ‘known pulmonary embolism or other deep venous thrombosis in patient’s medical history, without current anticoagulant therapy’ to the exclusion criteria after a SAE in the first patient enrolled in the study. The DSMB charter was modified to allow for ad hoc meetings at the request of PI. The patient information sheet was changed to include specific warning signs for (deep venous or arterial) thrombosis. The protocol was changed to allow local pharmacies to source IVMP and co-medication. The second amendment (2 July 2018) implemented a change of PI in the Radboud University Medical Centre. The third amendment (15 February 2019) included a cap on the total amount of IVIg administered (standard care) of 200 g, reflecting local practices in the UK. A range of appropriate dosing was added to reflect local practices regarding co-medication dosing the UK. A window of 2 days (earlier and later) was added in the planning of home care treatment scheduling. An emergency unblinding procedure was added. A 2- and 4-week window was added for the week 52 and week 104 study visits. Language was added to specify that hospital (or day care) admittance for further CIDP treatment (in case of a relapse, deterioration during treatment protocol) would not be considered a SAE. The fourth amendment (5 August 2019) further specified the text of two exclusion criteria (4 and 11) and added a further two (5 and 6) during the process of ethical approval in the UK. These additions were not made after a SAE or other safety concerns. In the fifth amendment (15 May 2020), changes to protocol were made to ensure safe study assessments in light of the COVID-19 outbreak. Enrolment of patients was temporarily stopped. Patients in the treatment phase of the trial were allowed to continued treatment. Study visits were allowed to be conducted as a telephone consultation, with questionnaires sent by mail or through Castor EDC. Week 18 and 52 visits were conducted by phone, in clinic or as home visits (the latter two if safety permitting). The amendment included a provision which allowed for a return to normal protocol when restrictive measures were (gradually) lifted. Screening logs were maintained during the temporary enrolment stop.

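### The primary outcome's 'sustained' clause joins the two disability scales with 'and/or' where the plan's own idea of no deterioration needs 'and'

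*Protocol article*

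**What the plan says.** All references are to the protocol article.

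- **Outcomes {12}, Primary outcome, general statement:** "Sustained is defined as no deterioration between 18 and 52 weeks".
- **Same paragraph, operational rule,** introduced as an explanation of that statement: "difference on the I-RODS of less than the MCID difference and/or less than one point on the adjusted INCAT-DS".
- **Same paragraph, improvement rule:** a gain of at least the MCID on the I-RODS, "and/or improvement of one or more points on the adjusted Inflammatory Neuropathy Cause and Treatment Disability Scale (INCAT-DS) at 18 weeks". Here *and/or* means that either scale is enough.
- **Same paragraph, failure criteria.** Criterion 3 covers patients who "restart CIDP treatment for any reason between 18 and 52 weeks". Criterion 4 covers those who "do not show a sustained improvement at 52 weeks as defined above", so it depends on the operational rule.
- **Participant timeline {13}:** after week 18, "treatment will be given only in case of deterioration by at least the MCID on the I-RODS and/or deterioration", continuing with "deterioration (i.e. increase) of at least one point on the adjusted INCAT-DS". Either scale is enough. This is a treatment trigger, but it is the article's only other scale-based statement of deterioration after week 18.
- **Discussion:** two scales were chosen because "relevant changes may be missed in patients if only one of these is used".
- **Long-term efficacy and safety evaluation:** remission at week 104 is to be analysed as at week 52.

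**The concern.** Deterioration on either scale is an 'or' condition. Its opposite, no deterioration, is that neither scale worsened, which is an 'and' condition. The sustained clause keeps *and/or* when it turns from change to absence of change. Taken at its word, it passes a patient who is two points worse on the adjusted INCAT-DS, provided the I-RODS loss stayed below the MCID. The same patient has deteriorated under Participant timeline {13}.

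This clause decides the primary endpoint through criterion 4. Two analysts, or two sites, could classify the same patient differently in good faith. If the choice were settled after unblinding, it would be a post-hoc choice of primary endpoint. If relapse is commoner on placebo, as the trial hypothesises, the lenient reading would tend to add more remissions to the placebo arm and dilute the difference.

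**Working it through.** **Step 1: the logic.** There are four possible patterns of relevant worsening from week 18 to week 52:

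| I-RODS worse | INCAT-DS worse | Deteriorated (Participant timeline) | Sustained, 'or' reading | Sustained, 'and' reading |
|---|---|---|---|---|
| no | no | no | yes | yes |
| no | yes | yes | **yes** | no |
| yes | no | yes | **yes** | no |
| yes | yes | yes | no | no |

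The 'and' column is the exact opposite of the deterioration column. The 'or' column disagrees with it in the two rows where only one scale worsened.

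**Step 2: who is affected.** Anyone who restarts treatment between weeks 18 and 52 fails under criterion 3, whatever the scales show. The readings therefore differ only for patients who improved at week 18, worsened on exactly one scale, and were still untreated at week 52. Table 1 schedules visits at weeks 24 and 52 with none between. Both scales are also recorded at unscheduled visits, which the treating physician may arrange if a relapse is suspected.

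**Step 3: the plan's sample size.** Inputs from Sample size {14}: 35% versus 65%, two-sided 0.05, 80% power.

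n = [1.96 × √(2 × 0.5 × 0.5) + 0.842 × √(0.35 × 0.65 + 0.65 × 0.35)]² / 0.30² = 42.4, so 43 per arm. Then 43/0.90 = 47.8, so 48 per arm. Both agree with the plan.

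Power = Φ[(d − 1.96 × √(2p̄(1 − p̄)/n)) / √((p₀(1 − p₀) + p₁(1 − p₁))/n)]

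- n = 43: (0.300 − 0.211)/0.103 gives 80.6%.
- n = 48: (0.300 − 0.200)/0.0974 gives 84.8%.

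**Step 4: illustration of size.** The documents give none of the following, so all are assumptions:

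- 35% and 65% are the rates under the 'and' reading;
- i is the share of an arm improved at week 18;
- u (10% to 40%) is the share of later relapses not retreated by week 52;
- s (30% to 60%) is the share of those worse on one scale only.

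Rate under the 'or' reading = p + (i − p) × u × s. In the central case with i = 75% in both arms, placebo is 0.35 + 0.40 × 0.25 × 0.50 = 40.0% and IVMP is 0.65 + 0.10 × 0.125 = 66.3%. In 48 patients this is 2.4 extra remissions on placebo and 0.6 on IVMP.

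Power at 48 per arm (84.8% without misclassification):

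| Improved at week 18, placebo / IVMP | u=10%, s=30% | u=25%, s=50% | u=40%, s=60% |
|---|---|---|---|
| 75% / 75% | 82% | 74% | 62% |
| 75% / 85% | 83% | 78% | 71% |
| 70% / 90% | 84% | 82% | 79% |

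The range is 62% to 84%. The low end depends on equal improvement in both arms, whereas the abstract's Discussion expects more patients to improve on the combination.

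**The case against.** The strongest reply is that the intent can be recovered. The governing statement is no deterioration, and the disputed words only explain it. Read with the Participant timeline and the stated reason for two scales, stability on both was almost certainly meant. That stands: a reader might infer that the plan deliberately adopts a lenient remission rule, and the documents do not support this. What remains is that the explanation is the operational rule, criterion 4 points back to it, *and/or* means either scale in the improvement rule of the same paragraph, and nothing in the article corrects it.

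A second reply is that few patients are exposed, because of criterion 3 and the unscheduled visits. This also stands, and it limits the size. It does not remove the contradiction, because one-scale worsening first found at week 52 is left to criterion 4 alone.

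Two stronger readings should be set aside:

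- A reader might infer that the improvement rule has the same fault. It does not. Gain on either scale is coherent, fits the reason for using two scales, and is repeated under Statistical methods, Secondary outcomes. Adding a condition on the other scale would be a new and stricter endpoint.
- A reader might infer from the undirected word 'difference' that further improvement breaks remission. The clause explains no deterioration, so worsening is meant. This needs only a change of wording.

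**Conclusion.** The sustained clause contradicts itself and two other sections. Under the literal reading, two of the four scale patterns are called sustained although the Participant timeline calls them deterioration. Because the clause decides the primary endpoint, and remission at week 104 after it, it should be corrected before unblinding.

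The size cannot be derived from the documents. The 62% to 84% power range rests wholly on assumed values of i, u and s, and on treating 35% and 65% as rates under 'and', which the Sample size section does not say. It shows that the effect could be trivial or material. It does not show that the trial is underpowered. A reader might infer an error in the sample size, but that calculation reproduces and is not in question.

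**What to change.** In Outcomes {12}, Primary outcome, replace the explanatory clause with, for example: *Sustained means that, relative to week 18, worsening is less than the MCID on the I-RODS and less than one point on the adjusted INCAT-DS. Relevant worsening on either scale is a failure under criterion 4; further improvement is not.* The existing exclusion of upper-limb changes between 0 and 1 continues to apply.

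Leave the either-scale improvement rule as it is. The treatment trigger in Participant timeline {13} needs no rewording, because the outcome clause would then agree with it. Carry the same definition into the week-104 analysis.

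The cost is one or two sentences in an amendment or the analysis plan, made while allocation is still blinded. No new data are needed. The downside is a slightly lower remission rate in both arms than the literal 'or' rule would give.
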